### Descriptive measures

Baseline self-reported descriptive measures include age, sex, gender, height, weight, body mass index (calculated from height and weight), ethnicity, geographical location determined based on residential postcode, education level, employment status, comorbidities assessed using the Self-Administered Comorbidity Questionnaire [40], symptoms in other joints, hip symptom duration, and pain medication usage.

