### Sample size 

We based the sample size on detecting a difference in change between-groups that meets or exceeds a specified minimal clinically important difference (MCID) for the two primary outcomes of hip pain on walking and WOMAC physical function. The MCIDs we used were 1.8 units for NRS hip pain [54] and 6 units for WOMAC physical function [55]. To achieve 80% power and a two-sided 5% significance level split equally across the two primary outcomes, assuming equal between-participant standard deviations of 2.5 for pain and 13 for function for both groups and a correlation between pre- and post-measurements of 0.25 for pain and 0.40 for function [56], and accounting for 15% loss to follow up, we required 91 participants per arm, for a total of 182 participants. We will consider the intervention to be effective if at least one of the two primary outcomes shows a significant between-group difference.

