### Data analysis plan

An a priori statistical analysis plan will be published on the Centre for Health, Exercise and Sports Medicine’s website. A statistician blinded to group details will perform analyses comparing the two groups. An intention-to-treat analysis will be conducted using data available from all randomised study participants. Multiple imputation will be conducted, and the method reported if the amount of missing data for either primary outcome is greater than 5%. The primary analysis will then use multiply imputed datasets, with a sensitivity analysis using complete case datasets.

A summary of participant demographics and baseline characteristics will be presented. Linear regression models, adjusted for baseline levels of the outcome, will be used to compare mean differences in change (baseline minus follow up) for continuous variables. Standard diagnostic plots will be used to assess model assumptions. Each primary outcome will also be dichotomised into those who do and do not achieve the MCID in improvement in hip pain on walking and function to aid clinical interpretation of results. For these and other binary outcomes, groups will be compared using risk differences and risk ratios, calculated from logistic regression models and adjusted for the outcomes at baseline where available.

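### The stated models adjust each outcome only for its own baseline; this is valid and matches the sample size, but a few baseline measures already collected could be added at almost no cost

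*Protocol article*

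**What the plan says.** The Data analysis plan fixes the model for continuous outcomes: "Linear regression models, adjusted for baseline levels of the outcome, will be used" to compare the groups on mean change, taken as baseline minus follow-up. It names no other covariate. Binary outcomes are compared by risk differences and risk ratios from logistic models, "adjusted for the outcomes at baseline where available".

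The Sample size section assumes "a correlation between pre- and post-measurements of 0.25 for pain and 0.40 for function" and divides the type I error between the two primary outcomes: "a two-sided 5% significance level split equally across the two primary outcomes". Success requires a significant difference on at least one of them.

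Table 1 and the Descriptive measures section list further data taken before allocation. These include both primary outcomes, BMI, comorbidities and "symptoms in other joints, hip symptom duration, and pain medication usage". In Table 1 the two global ratings and oral pain-medication use for hip pain are marked at 24 weeks only. Medication usage appears at baseline as a separate descriptive item.

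The Randomisation section describes permuted blocks and names no stratification factor.

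**The concern.** On the protocol's own assumptions, each outcome's baseline explains little of its 24-week value: 0.25² = 6.25% of the variance for pain and 0.40² = 16% for function. Baseline function is available for the pain model and baseline pain for the function model, but neither crosses over as the plan is worded.

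For binary outcomes the own-baseline rule has two soft spots. The global ratings measure change since baseline, so they have no baseline value and would be unadjusted. For pain medication, a baseline item exists but is listed separately from the 24-week outcome. It is unclear whether it counts as the outcome's baseline.

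What is at stake is precision, chiefly for function, which determines the sample size and has no margin. Validity is not at stake.

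**Working it through.** **Inputs, all from the Sample size section.** "assuming equal between-participant standard deviations of 2.5 for pain and 13 for function for both groups"; pre-post correlations 0.25 and 0.40; "The MCIDs we used were 1.8 units for NRS hip pain [54] and 6 units for WOMAC physical function [55"]; alpha 0.05/2 = 0.025 two-sided per outcome; 80% power; 15% loss to follow-up.

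**Step 1: reproduce the plan's figure.** With own-baseline adjustment, residual SD = SD × √(1 − r²).

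- Function: 13 × √0.84 = 11.91. With a noncentral t calculation, a difference of 6 and alpha 0.025, 77 completers per arm give 80.4% power. Then 77/0.85 = 90.6, rounded up to 91, which is the stated number. (The normal approximation gives 75 completers and 89 enrolled.)
- Pain: 2.5 × √0.9375 = 2.42. A difference of 1.8 needs only 36 completers per arm. With 77 per arm, power is 99.0%.

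Other models do not reproduce 91. Under the normal approximation, an unadjusted change score for function needs 128 per arm and an unadjusted follow-up score needs 106, both after allowing for loss. The trial was therefore sized on the own-baseline model that the analysis section states.

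**Step 2: what further covariates could add for function.** The document gives no prognostic strength, so the extra R² is an assumption, expressed as a share of total variance.

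- Residual SD = 13 × √(0.84 − extra R²)
- Standard error (SE) = residual SD × √(2/77)
- Equivalent gain in participants = 0.84/(0.84 − extra R²) − 1

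| Assumed extra R² | Residual SD | SE (WOMAC points) | Power | Equivalent gain in participants |
|---|---|---|---|---|
| 0 | 11.91 | 1.92 | 80.4% | 0% |
| 3% | 11.70 | 1.89 | 82.0% | 4% |
| 5% | 11.55 | 1.86 | 83.0% | 6% |
| 10% | 11.18 | 1.80 | 85.5% | 14% |

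**Step 3: the same for pain.** At an extra R² of 10%, the residual SD is 2.5 × √(0.9375 − 0.10) = 2.29, and power goes from 99.0% to 99.5%. That is not material.

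**Step 4: the success rule.** Power for at least one significant primary outcome cannot be lower than power for pain alone. It is therefore already at least 99.0% under the planning assumptions, and covariates can hardly raise it.

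**Step 5: the cost if a covariate is useless.** Each added covariate uses one of 2 × 77 − 3 = 151 residual degrees of freedom. That alone leaves function power at 80.4%. An unprognostic covariate also inflates the variance slightly through chance imbalance. With N = 154 and k added covariates, the inflation averages about k/(N − k − 3). For one covariate this is 1/150 = 0.7%, and function power becomes about 80.1%.

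**Step 6: binary outcomes, by reading.** The 24-week medication outcome is defined by named oral drug classes taken at least weekly in the prior month for hip pain. The baseline item is described only as medication usage (Table 1) or pain medication usage (Descriptive measures). The article does not say that the two share a definition, so the rule can be read either way. For the global ratings there is nothing to adjust for under the rule as written, although baseline pain and function are recorded.

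**The case against.** The strongest objection is that nothing is wrong. Regressing change on the outcome's own baseline is a standard, valid analysis. It is the model the trial was sized on, and it delivers the promised power. All of this stands, and Step 1 confirms it.

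A reader might infer from the 6% and 16% that the plan throws away precision, as though other baseline variables would explain the remaining 94% and 84%. The documents do not support that. A weak pre-post correlation shows only that the own baseline predicts little. It says nothing about other variables, and their added R² may be zero. For the same reason no case can be made from the document that BMI, symptom duration or symptoms in other joints belong in the model.

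It can also be said that the promised statistical analysis plan may add covariates, that the imputation model can hold auxiliary variables whatever the analysis model contains, and that randomisation with a correct confidence interval already allows for chance imbalance. Each of these is right. Imbalance is therefore not a second defect beside precision. The point survives only because the protocol states a specific adjustment rule, and that rule can be improved with data already in hand.

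On pain medication, a reader might conclude that the outcome will go unadjusted. The text does not say so. The baseline item may well be what the rule has in mind, and the article leaves this unclear.

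**Conclusion.** The point holds as an inexpensive improvement to a stated rule. It does not show an error, a contradiction or a loss of planned power. The benefit is confined to function: from nothing to about 5 percentage points of power (80.4% to 85.5%) for an assumed extra R² of 0 to 10% of total variance. That range is an assumption throughout. The calculation also takes the protocol's SDs, correlations and 15% loss as true, and the table does not deduct the small variance inflation in Step 5. Pain gains nothing material, and the overall success criterion is almost unaffected. For the binary secondary outcomes the gain cannot be quantified from the document; there the main value is a rule that reads only one way.

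**What to change.** Before group codes are seen, write into the analysis plan:

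1. Both primary models include baseline walking-pain NRS and baseline WOMAC function.
2. Oral pain-medication use at 24 weeks is adjusted for baseline pain-medication usage, with the baseline variable defined explicitly.
3. The two global ratings are adjusted for baseline pain and baseline function.
4. The imputation model contains the same covariates, and the own-baseline model is kept as a sensitivity analysis.

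Further covariates, such as BMI, symptom duration or symptoms in other joints, are optional. If any are used, the list should be short and fixed in advance.

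The cost is wording only, since all these data are collected before randomisation. The statistical price is one degree of freedom per added covariate, plus slight variance inflation where a covariate proves unprognostic (about 0.3 percentage points of function power for one).

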### Timelines

Ethical approval for the trial was given by The Human Research Ethics Committee of The University of Melbourne on 19^th^ September, 2022. We prospectively registered the trial with the Australian New Zealand Clinical Trials Registry on 12^th^ December, 2022. Participant recruitment started in March 2023. Recruitment is anticipated to be completed in September 2024. The main trial is scheduled for completion in March 2025 with all participants completing 24 week data collection.

### Dissemination

We will disseminate study findings through conference presentations and publication in peer-reviewed journals as well as via our Centre website, knowledge translation network, media and social media, including a study infographic. We will follow the International Committee of Medical Journal Editors recommendations for authorship.

## Discussion

This protocol describes the background, aims and methods for a two-group, parallel design RCT aiming to evaluate the effectiveness of a self-directed unsupervised digital exercise intervention on the two primary outcomes of change in hip pain while walking and physical function at 24 weeks, compared with a digital education-only control for people with hip OA. The effects of the intervention on other clinical outcomes at 24 weeks will also be evaluated. A range of measures will provide information about the safety and acceptability of, and engagement with, this program that focuses on core recommended hip OA treatments of education and exercise/physical activity. Such a program has the potential to enhance patient access to evidence-informed lifestyle treatments and reduce the personal and societal burden of OA.

## Data Availability

The datasets used and/or analysed during the current study will be made available from the corresponding author on reasonable request.
